#### Primary outcome measurements

Blood pressure will be the primary outcome of this trial. The CRC will assess the participant’s blood pressure in a stable state using an automatic electronic blood pressure monitor (HBP-1300, Omron Dalian Co., Ltd., China). To obtain accurate data, the measurements will be conducted three times and their mean value will be used as the outcome. Blood pressure will be measured at baseline (assessment 1), prior to each of the visits (assessments 2 and 3), and during the follow-up visit (assessment 4). The primary endpoint is week 8 (assessment 3).

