### Sample size

This study took into account the results of a previous study [18] that used taichi as the main evaluation index. The calculated sample size necessary for the *t*-test was 36 subjects in each group, which was conducted with a G power analysis with an effect size of 0.67, test power of 0.80, and significance level of 0.05. Considering a dropout rate of 10%, we aim to recruit a total of 40 subjects in each group.

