### Statistical analysis plan

Continuous variables will be expressed as mean ± standard deviation, and categorical variables will be expressed as *n* (%). The demographic baseline information (age, gender, occupation, past history, present illnesses, and medications) will be tested using the chi-squared test and independent *t*-test.

As the primary statistical analysis, the effectiveness of taichi will be tested by calculating the differences in the maximum SBP and minimum DBP before (baseline) and after (week 8) treatment for each test subject. Comparisons of the within-group differences will be performed using a paired *t*-test and between-group differences using an independent *t*-test. If the data do not have a normal distribution, they will be tested using a nonparametric test (a Wilcoxon signed-rank test or Wilcoxon rank-sum test).

The heart rate and the body composition of the participants will be tested to verify the effectiveness of taichi by calculating the difference between before (baseline) and after (week 8) the treatment as described above.

The results of the questions regarding the intensity and difficulty of the exercises will be evaluated by the researchers, and the numerical value will be analyzed by a simple descriptive statistical method. We will perform a simple correlation analysis or simple regression analysis to determine whether there is a correlation between the differences in blood pressure and the intensity and difficulty of the exercise as perceived by the experimental group.

Information regarding adverse events will be collected through patient reports and researchers’ observations. The frequency of adverse events will be analyzed by a chi-squared test or Fisher’s exact test.

All statistical analyses will be conducted in a two-sided manner, with a significance level of 5%. In addition, we will use an intention-to-treat analysis for missing data in the primary and secondary analyses. The last-observation-carried-forward and multiple imputation, which are widely used in clinical research, will be applied to missing data and additional multiple imputation or regression analysis will be used to check any differences.

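### SBP and DBP share the primary analysis, each at an unadjusted two-sided 5%, with no rule for what counts as success and a sample size for one unnamed variable

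*Protocol article*

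**What the plan says.** All references are to the protocol article.

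- **Primary outcome measurements:** "Blood pressure will be the primary outcome of this trial". The section sets week 8 as the primary time point but does not choose between systolic and diastolic pressure. The primary-outcome field of the registration data set (Table 2) also gives only blood pressure, and lists all assessment times without singling out week 8.
- **Statistical analysis plan:** in the primary analysis, "the effectiveness of taichi will be tested by calculating the differences in the maximum SBP and minimum DBP" from baseline to week 8. The arms are compared as "between-group differences using an independent *t*-test", with a rank-sum test as the non-normal alternative. The level is then set for everything: "All statistical analyses will be conducted in a two-sided manner, with a significance level of 5" per cent.
- **Sample size:** a t-test with "effect size of 0.67, test power of 0.80, and significance level of 0.05", giving "36 subjects in each group" and 40 per arm after 10% dropout. The variable behind the effect size is not named.

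No section ranks the two pressures, gives a success rule or adjusts for two tests.

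**The concern.** The design budgets for one test at 5%, while the primary analysis runs two. With no success rule, a mixed result (one pressure significant, the other not) could be called positive or negative after the data are seen. The Blinding section relies on a blinded analyst to guard against selective reporting of outcomes. Not knowing the allocation does not stop anyone choosing between SBP and DBP once both p-values exist; only a rule fixed in advance does that.

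What is at stake depends on the rule eventually applied. An either-pressure rule breaks the stated 5%. A both-pressures rule keeps the 5% but does not have the stated 80% power.

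**Working it through.** **Inputs from the article.** Effect size d = 0.67, alpha 0.05 two-sided, power 0.80, 36 evaluable per arm, 10% dropout, two primary variables, one primary time point, no interim analysis.

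**Assumed.** The correlation r between a participant's SBP change and DBP change, which is also approximately the correlation between the two test statistics. The article gives no value, so a range is shown. For joint power, d = 0.67 is assumed for both pressures.

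**1. The plan's own figure.** For a two-sample t-test the noncentrality is d × √(n/2) = 0.67 × √18 = 2.843, with 70 degrees of freedom and a critical value of 1.994. Power is 80.05%. Solving for 80% gives n = 35.96, so 36 per arm; 36 / 0.90 = 40. The stated figures reproduce as one two-sided 5% test. A one-sided test would need only 29 per arm.

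**2. Either pressure counts.** With no true effect, the chance of at least one significant result is 1 − P(|Z₁| < 1.96 and |Z₂| < 1.96), with Z₁, Z₂ bivariate normal with correlation r. At r = 0 this is 1 − 0.95² = 9.75%, which is also the maximum over r.

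| r | At least one false positive |
|---|---|
| 0 | 9.75% |
| 0.5 | 9.1% |
| 0.6 | 8.8% |
| 0.7 | 8.3% |
| 0.8 | 7.8% |
| 0.9 | 7.0% |

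**3. Both must be significant.** A false claim needs a false positive on at least one pressure that has no effect, so type I error is at most 5%. Simulated two-sample t-tests at n = 36 and d = 0.67 on both give joint power of about 69% at r = 0.5 and 71% at r = 0.7. A normal approximation runs slightly higher, at 70% and 73%. By that approximation, 80% joint power needs 44 per arm at r = 0.5 and 42 at r = 0.7. After 10% dropout these become 44 / 0.90 → 49 and 42 / 0.90 → 47.

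**4. Either counts, with alpha split (0.025 each).** Power per pressure at 36 per arm is 70.9%. The relevant quantity for this rule is power for at least one win. By simulation that is about 85% at r = 0.5 and 82% at r = 0.7.

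**5. If the second pressure responds less.** Power at 36 per arm for one 5% test is 71% at d = 0.6, 55% at d = 0.5 and 39% at d = 0.4.

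**The case against.** **The rest may be in an unseen analysis plan.** A journal article may leave a success hierarchy to a fuller document. That would answer a complaint about silence alone. Here, however, the article puts both pressures in the primary analysis and fixes 5% for all tests. A later plan could split alpha only by overriding that sentence.

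**The inflation is limited.** There is one time point, one between-group test per pressure, no interim look, and two positively related measures in an 80-patient, single-centre trial. This stands: the rate cannot exceed 9.75% and falls as the correlation rises.

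**Stronger readings that the article does not support:**

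- A reader might infer that the false-positive rate simply is 8–9%. That needs an either-pressure rule, which the article does not state, and a correlation of about 0.5 to 0.75, which it does not give.
- A reader might infer that 80% power holds for only one of the two pressures. If d = 0.67 applied to both, each test would have 80%. What can be said is that the calculation supports one unnamed variable and gives no basis for the other.
- A reader might infer that splitting alpha necessarily costs the trial its 80%. Power for each pressure does fall to 71%, but power for at least one win stays above 80% at r = 0.5–0.7.
- A reader might assume that 0.67 is a systolic effect. The Sample size section does not say so, and the Discussion describes the source study as covering waist circumference as well as blood pressure.

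**Preferring SBP is a choice.** This also stands. Eligibility can be met on either pressure, so the article does not point to a lead variable.

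**Conclusion.** The point holds. Two variables share the primary analysis at an unadjusted 5% each, success is undefined, and the sample size is for one test on an unidentified variable.

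- **Either rule:** the false-positive rate is up to 9.75%, and about 9.1% to 7.0% for an assumed r of 0.5 to 0.9.
- **Both rule:** type I error is at most 5%, with joint power of about 69–71% for r = 0.5–0.7 and d = 0.67 on both.
- **One named pressure:** 5% and 80% both hold at 36 per arm, provided 0.67 is a fair effect size for that pressure.

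The 36 and 40 per arm are correct arithmetic for a single test. The defect lies in what that test is meant to be.

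**What to change.** Before unblinding:

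1. Name the between-group difference in change from baseline to week 8 in one pressure (for example SBP) as the single primary endpoint at two-sided 5%. Test the other pressure, also at 5%, only if the first is significant. Alternatively, state an either rule or a both rule, with the matching alpha and a restated power.
2. State which variable the 0.67 came from. If it is not the chosen primary, restate the power for the one that is.
3. Enter the same hierarchy and the week-8 time point in the registry's primary-outcome field.

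**Cost.** Wording in the protocol and registry. With one named primary the sample size need not change, if 0.67 applies to it. A both rule at 80% power would need about 47–49 recruited per arm for r = 0.7–0.5, instead of 40. The small downside of the fixed sequence is that an effect on the second pressure alone can no longer be claimed as confirmatory.

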### Safety

Because the intervention is a simple exercise rather than untested drugs or medical devices, we do not expect any adverse events will be caused by the general Korean medical treatment. However, the investigators will inform the participants of all possible adverse events that may occur after taichi and instruct them to report any such adverse events. All adverse events recorded during the research period will be analyzed and reported. In general, due to the interventional characteristics of exercise, simple muscular pain may occur. We will provide beverages such as bottled water or green tea during the exercise sessions for the participants. To prevent falls and severe muscle aches, a chair will be available during exercise sessions. There will also be a space where participants can sit and relax. If a direct injury occurs in connection with this study, appropriate medical action may be taken, as determined by the investigator.

A data monitoring committee (DMC) comprising members of staff from the clinical research service institution (Woosuk University) will periodically monitor the study by telephone, e-mail, and visits, if necessary. The DMC will be composed of one statistician and one specialist in clinical research methodology. They will review the progress of the study and check all case report forms. In addition, they will check whether the study has followed the study protocol. If a problem is identified, the DMC will modify the protocol if necessary. If modifications to the protocol are required during the study, the modified protocol will be submitted by the clinical trial review committee to the IRB for approval. However, neither auditing nor an interim analysis are planned during the trial.

Additionally, as we will not collect any biological samples and do not intend to use the participants’ data in future studies, we do not need any additional consent for collection and use of participant data or biological specimens in ancillary studies. In accordance with government regulations and standards, all documents related to the conduct of a clinical trial must be kept by the director of clinical research, or the director of the institution and the clinical research manager, for at least 3 years after the completion of the clinical trial.

### Ethics and dissemination

As this clinical study was prepared with patient rights and well-being in mind based on the Declaration of Helsinki, the clinical researchers will follow the research plan and will actively respond to any problems raised by the participants. Additional file 1 contains a completed SPIRIT checklist.

Before patients are asked to participate in this clinical study, the researchers will explain to them all the details of the research. They must voluntarily agree to participate in the research. The English initials of the names of the participants in the trial will be recorded and identifying information will be managed using a subject identification code list to prevent personal information, such as social security numbers, from being leaked. Other researchers and research organizations will be able to view the clinical research data collected during reviews by the DMC, IRB inspections and assessments, and government surveys. On completion of the trial, the researchers will consult with the clinical research service institution (Woosuk University) to prepare a report of this study. The study findings will be disseminated in peer-reviewed journals and presented at national and international conferences. Additionally, we will share deidentified individual patient data. The datasets used or analyzed during the study can be requested from the corresponding author.

## Discussion

When searching for research conducted in Korea into the effects of taichi on blood pressure, we found studies that assessed the effects of taichi on waist circumference and blood pressure of the elderly [18] and the effect of taichi on the cardiac autonomous nervous system and blood pressure of elderly women [16]. These studies on taichi mainly had elderly participants. In addition, in a systematic review by Hwang et al. [19], only randomized controlled trials from China, Italy, United Kingdom, USA, Hong Kong, and Taiwan were analyzed, and no randomized controlled trials from Korea were included.

A major limitation of this study is that the participants cannot be blinded due to the nature of the intervention. Because the experimental group has to perform taichi, the participants will know whether they belong to the experimental group or the comparator group. This knowledge may affect the results of the study by influencing other behaviors, which may, thus, differ between the groups.

A strength of this study is that it will evaluate the effects of taichi in ordinary adults aged 19 to 70 years instead of being limited to the elderly. In addition, this study is a randomized controlled trial of taichi, which is not widely practiced in Korea. Taichi is easy to perform and not strenuous, so it can easily be practiced at home by almost anyone. As a result, this study may provide valuable data on the effects of taichi on hypertension.

### Trial status

The current protocol is version 1.7, dated 28 November 2019. Recruitment began on 17 April 2019. The approximate completion date for recruitment is in April 2020. This trial was prospectively registered before recruitment began.

## Data Availability

The datasets used or analyzed during the study can be requested from the corresponding author.

## Abbreviations

CRC: Clinical research coordinator
DBP: Diastolic blood pressure
DMC: Data monitoring committee
IRB: Institutional review board
PNUKH: Pusan National University Korean Medicine Hospital
PNUYH: Pusan National University Yangsan Hospital
SBP: Systolic blood pressure
